### Study status and timeline

Recruitment began on June 20, 2026, and is currently ongoing. Participant recruitment is expected to be completed by June 2028, data collection by December 2028, and the primary study results are expected by June 2029.

### Success criteria

The success of this study will be assessed quantitatively based on the achievement of its primary and secondary objectives. Success will be evaluated across three domains: efficacy, tolerability, and safety, based on changes in HAM-D-17 scores, participant retention and protocol adherence, and the frequency and nature of AEs and SAEs. Specifically, success will be indicated by a clinically meaningful reduction in HAM-D-17 scores, defined as a reduction of ≥50% from baseline, in the active FES group. Additionally, a statistically significant difference in HAM-D-17 score changes between the active and sham groups will be required. Successful tolerability will be demonstrated by a dropout rate of ≤15% and high adherence to the treatment protocol, with at least 85% of participants completing all scheduled FES sessions.

For safety outcomes, the number, nature, and duration of AEs will be evaluated in both active and sham groups, and no significant differences between groups in AE frequency or severity will indicate successful safety outcomes. Additionally, the sustainability of observed treatment effects will be assessed by analyzing HAM-D-17 response and remission rates, as well as changes in secondary outcomes, including anxiety (GAD-7), quality of life (WHO-5), and sleep quality (PSQI) over the four-week follow-up period. Sustained improvements across these domains in the active group, without significant increases in adverse effects, will further validate the success of the study.

If these success criteria are met, the findings will provide a robust foundation for designing a large-scale, multisite RCT to further evaluate FES for MDD.

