A neural feedback loop has been proposed in which facial muscle activity influences emotional processing through the amygdala, a key structure involved in emotion processing and generation [15]. Facial motor activity is conveyed to the amygdala, which integrates proprioceptive signals from the trigeminal nerve and interoceptive signals carried through the glossopharyngeal and vagus nerves [15]. By activating the facial muscles, FES may engage these pathways and contribute to neuroplastic changes involved in emotional regulation.

Zariffa et al. (2014) [14] conducted a pilot study exploring the mood-related effects of a single FES session targeting the Duchenne smile muscles in healthy individuals. Twelve participants receiving FES were compared with 12 controls. Based on the Positive and Negative Affect Schedule-X (PANAS-X), the findings suggested that FES may influence emotional states such as feeling “determined,” “daring,” “scared,” and “concentrating.” Building on this initial study, Kapadia et al. (2019) [16] conducted an open-label trial with MDD patients and reported significant improvements in depressive symptoms following a treatment course with FES, with participants showing an 8.1-point reduction on the 17-item Hamilton Depression Rating Scale (HAM-D-17) and a 14-point reduction on the Inventory of Depressive Symptomatology after 10 sessions of FES. Moreover, evidence from studies on Facial Neuromuscular Electrical Stimulation (fNMES), which directly activates facial muscles using computer-controlled electrical impulses, also supports an effect of facial muscle activation on emotional experience [17,18]. Participants reported more positive emotions after stronger stimulation of the zygomaticus major (smile muscle) compared to the depressor anguli oris (frown muscle) [18]. These studies provide promising evidence for the therapeutic potential of FES for MDD, setting the stage for designing a rigorous randomized sham-controlled trial (RCT) examining the efficacy of repetitive FES of facial muscles for MDD. This pilot RCT will assess the efficacy, safety, and tolerability of 20 sessions of FES in 60 participants diagnosed with MDD using a sham-controlled design.

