### Objectives

The primary objective of this RCT is to evaluate the efficacy, tolerability, and safety of FES targeting the Duchenne muscles in participants with MDD. We hypothesize that participants receiving active FES will show greater reductions in the HAM-D-17 [19] total score than participants receiving sham FES with no significant differences in dropout rates, protocol adherence, or the incidence of adverse events (AEs) and serious adverse events (SAEs) between the two groups.

A secondary objective of this RCT is to evaluate the impact of FES on MDD response and remission rates, anxiety, quality of life, sleep quality, and the sustainability of these effects over four weeks. We hypothesize that participants receiving active FES will show significantly greater improvements across all these domains compared to those receiving sham FES.

A further objective of this RCT is to explore changes in facial expressivity during a semi-structured emotional recall interview using objective facial coding. We hypothesize that participants receiving active FES will demonstrate greater frequency, intensity, and duration of Duchenne smiles than those receiving sham FES during emotional recall interviews, reflecting enhanced emotional expressivity.

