### Sample size

The sample size calculation is based on a between-group comparison of the mean change in HAM-D-17 scores from baseline to day 20. Analysis of covariance (ANCOVA) will be used, with the change in HAM-D-17 score from baseline to day 20 as the outcome and baseline HAM-D-17 score and sex as covariates. In our previous pilot study [16], involving 10 participants with moderate to severe MDD who received three FES sessions per week (ranging from a minimum of 10 to a maximum of 40 total sessions), FES demonstrated a moderate to large effect size (d = 0.6–1.2) in MDD. All 10 participants completed the required 10 sessions, and 5 participants completed 40 sessions [16]. Our RCT will use 20 sessions of FES, which was well tolerated in research on rTMS for MDD and FES for stroke and spinal cord injury rehabilitation.

A total of 60 participants (30 in the active arm and 30 in the sham arm) is planned to detect a clinically meaningful between-group difference in HAM-D-17 scores, assuming a moderate effect size of 0.5 (Cohen’s d), a two-tailed significance level of 0.05, and 80% power. Accounting for a 15% attrition rate, approximately 51 participants are expected to complete the study, exceeding the recommended minimum sample size (24–50 participants) needed to generate reliable estimates of the standard deviation and correlation of HAM-D-17 scores for future sample size calculations in a definitive trial. Furthermore, a sample size of 60 will allow the anticipated 15% dropout rate to be estimated with an approximate 95% confidence interval margin of error of ±8.4. As the first proof-of-concept RCT of its kind, this trial is designed primarily to detect a signal for the primary outcome, change in HAM-D-17 over time. We recognize that the proposed sample size may not provide high statistical power for some secondary and exploratory outcomes.

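### The success criteria add an uncontrolled, undefined 50% fall in the active arm to the required sham comparison, and they judge sustainability without reference to sham

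*Protocol article*

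**What the plan says.** Protocol article, Success criteria. Efficacy success is indicated by a clinically meaningful fall in HAM-D-17, "defined as a reduction of ≥50% from baseline, in the active FES group". The next sentence adds that "a statistically significant difference in HAM-D-17 score changes between the active and sham groups will be required". The two conditions apply together.

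The same section handles durability over the four-week follow-up as follows: "Sustained improvements across these domains in the active group, without significant increases in adverse effects, will further validate the success of the study". Sham is not mentioned in that sentence. The section closes by linking the criteria to the next trial: "If these success criteria are met, the findings will provide a robust foundation for designing a large-scale, multisite RCT".

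Elsewhere the plan is comparative. The secondary objective covers response, remission, anxiety, quality of life, sleep and the durability of these effects, and its hypothesis is that "participants receiving active FES will show significantly greater improvements across all these domains compared to those receiving sham FES". The Data analysis plan compares HAM-D-17 change between arms by ANCOVA adjusted for baseline score and sex, foresees similar analyses for secondary clinical outcomes, and uses odds ratios for response and remission. Outcome measures and data collection defines response as a 50% decrease in the HAM-D-17 total, a definition that applies to an individual participant.

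**The concern.** A fall from baseline within one arm mixes the effect of stimulation with everything else that happens over four weeks: natural course, regression to the mean, expectation, and the comedy video and deliberate smiling that the Intervention section places in the sessions. Whether that total reaches half of baseline depends on how ill the participants are at entry and how much they would have improved anyway. Neither tells us whether active stimulation beats sham.

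The condition also cannot be applied as written. It could mean that the mean fall in the arm is at least half the mean baseline, or that enough participants each fall by half. In the second case no share is given. The two readings can disagree on the same data, because an arm can hold many responders while its mean fall stays below half.

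For sustainability the gap is wider, because that sentence contains no comparison at all. Depression often improves over eight weeks without specific treatment, so improvement that lasts in the active arm could be declared a success even if sham participants did equally well.

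At stake is how clearly the pilot can support a larger trial, which is the stated use of these criteria.

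**Working it through.** **1. Inputs from the protocol.** 60 randomised, 30 per arm; 15% attrition, so 60 × 0.85 = 51 completers as the protocol states, or 25.5 per arm; planning effect d = 0.5; two-sided 5% (Sample size). Entry requires MADRS ≥7, and no HAM-D-17 floor is stated (Eligibility criteria). The Introduction reports "participants showing an 8.1-point reduction on the 17-item Hamilton Depression Rating Scale" after 10 sessions in an open-label trial.

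**2. The threshold against the earlier trial.** On the arm-mean reading, a fall of 8.1 points is at least 50% only if mean baseline ≤ 8.1 / 0.5 = 16.2. At assumed mean baselines of 14, 18 and 20 the same fall is 8.1/14 = 58%, 8.1/18 = 45% and 8.1/20 = 40.5%. This is arithmetic only. The article gives neither the baseline mean nor the SD of change for that trial, and the figure is for 10 sessions rather than 20, so no pass probability can be attached to it without further assumptions.

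**3. Both conditions together.** Assumptions, none of them in the protocol: SD of change 7, baseline SD 4, baseline and change independent, mean baseline 12 to 24, mean sham fall 4 to 10 points. There were 26 per arm and 20,000 simulated trials per setting. The 50% condition was read as mean active fall ≥ half of mean active baseline. The between-arm condition was a two-sided t-test at 5% favouring active, which is simpler than the planned ANCOVA.

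| Mean baseline / sham fall | 50% condition alone, no effect | Both, no effect | 50% condition alone, d = 0.5 | Both, d = 0.5 |
|---|---|---|---|---|
| 12 / 10 | 99.8% | 2.4% | 100% | 42.5% |
| 16 / 7 | 24.5% | 2.3% | 96.2% | 42.5% |
| 16 / 4 | 0.2% | 0.1% | 36.5% | 26.9% |
| 20 / 7 | 1.7% | 0.6% | 63.9% | 37.2% |
| 20 / 4 | 0.0% | 0.0% | 4.1% | 3.8% |
| 24 / 4 | 0.0% | 0.0% | 0.1% | 0.1% |

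The between-arm test alone passed 42–43% of the time at d = 0.5 in every setting. Over the whole grid, the highest joint pass rate with no effect was 2.7%, within simulation error of the nominal 2.5%.

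Hand check for 20 / 4 at d = 0.5: expected active fall 4 + 0.5 × 7 = 7.5; threshold 20/2 = 10; standard error √[(7² + (0.5 × 4)²)/26] = √(53/26) = 1.43; P = 1 − Φ(2.5/1.43) = 1 − Φ(1.75) = 4.0%, against 4.1% simulated.

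The 42–43% is below the protocol's stated 80% power. That is a separate question about the sample size. Here the figure serves only as a constant reference.

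**4. Reading the table.** With mild baselines and a large sham response, the 50% condition is met whether or not the treatment works, so it adds nothing. With higher baselines and a small sham response, it decides the result and overrides the comparison with sham.

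**5. Sustainability.** The objective compares durability in active with sham. The criterion looks at the active arm alone. A trial with identical, lasting improvement in both arms meets this criterion and fails the hypothesis.

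**The case against.** A reader might infer that efficacy is judged on within-arm change, so that a large placebo response could carry the trial to success. The text does not support that. The sham comparison is explicitly required, the primary analysis is between arms, and the joint false-pass rate stays at about 2.5% or less.

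A reader might also infer that missing the 50% threshold blocks a multisite trial. The section says only what follows if the criteria are met, and the abstract says without condition that the findings will guide a larger trial. The harm is a result that misses its own stated success criteria, not a binding stop.

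Nor is there a flat contradiction in the use of clinical meaningfulness. The Sample size section says the number "is planned to detect a clinically meaningful between-group difference in HAM-D-17 scores", whereas the Success criteria concern a fall from baseline. These are different quantities, although sharing one label is unhelpful.

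Requiring both superiority over sham and a substantial absolute response is a legitimate kind of benchmark, and the full protocol in S2 File, not shown here, may define the threshold. Both points have weight. They do not remove the dependence on case mix, and a benchmark that can be read in two ways is not yet usable.

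On sustainability, the wording is supportive (it further validates success), and the Data analysis plan offers between-arm methods for the same outcomes. That lowers the severity. It does not put sham into the criterion, which is the sentence that will be applied.

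**Conclusion.** The point holds in limited form. The required sham comparison protects against a false efficacy pass. What remains is an additional active-arm threshold that is uncontrolled and not defined as a mean or a responder share, so that the same between-group effect can meet or miss the criteria for reasons unrelated to efficacy. The firm figure is the 16.2-point mean baseline above which the earlier trial's 8.1-point fall is no longer 50%, on the arm-mean reading. The simulated range of about 0.1% to 43% joint success at d = 0.5 shows the direction and possible scale. It rests on an assumed SD of change, baseline and sham response and should not be quoted as this trial's operating characteristics. No calculation is possible for the responder-share reading, because no share is given.

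The sustainability criterion does not match the stated hypothesis and could be satisfied by natural recovery. This needs no numerical assumption. Both matters should be settled before unblinded data are seen.

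**What to change.** Efficacy: base success on the adjusted active-minus-sham difference in HAM-D-17 change with its 95% CI, from the ANCOVA already planned, together with the active-minus-sham difference in the proportion with a ≥50% reduction, using the protocol's own response definition. Report the percentage fall within the active arm descriptively.

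If an absolute-response condition is kept as well, state whether it is an arm mean or a responder share, give the share if so, and say how a trial that meets only the sham comparison will be described.

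Sustainability: word the criterion as the active-minus-sham difference in response, remission and the secondary outcomes at the follow-up visits, using the ANCOVA and odds-ratio methods of the Data analysis plan.

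Cost: a rewording plus a small amount of extra analysis, because the ANCOVA is currently described only up to the final session. No new data are needed, since HAM-D-17 and the secondary outcomes are collected in both arms at baseline, weekly and at follow-up. The sustainability claim becomes harder to meet. Recruitment is planned to run to June 2028 and results are expected by June 2029, so there is time to amend before unblinding.

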### Randomization and masking

Participants will be randomly assigned in a 1:1 ratio to receive either active FES or sham using a randomization schedule generated through a secure REDCap module. Block randomization, stratified by sex, will account for potential differences in response and tolerability. Personnel conducting outcome assessments and other blinded study procedures will not have access to the fixed block size or treatment assignments. Randomization will be conducted by the intervention staff, who will have access to group assignments as required to deliver and monitor the stimulation sessions. In an emergency, the study doctor may be informed of the participant’s group assignment if this information is necessary for clinical management.

Moreover, to preserve blinding, sensory and non-Duchenne-patterned sham stimulation will be utilized. Participants will be instructed to avoid interaction with one another throughout the study. Blinding effectiveness will be assessed after each session by asking participants and raters to indicate whether they believe the participant received active or sham FES.

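### The safety success criterion treats a non-significant AE comparison as evidence of safety, with no margin and no AE power; at 30 per arm it would more often than not pass a doubled AE rate if the sham rate is up to about 25%

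*Protocol article*

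**What the plan says.** The Success criteria section names three domains: efficacy, tolerability and safety. For safety, the number, nature and duration of AEs are evaluated in both arms, and the deciding sentence is that "no significant differences between groups in AE frequency or severity will indicate successful safety outcomes". The same section later counts sustained improvement without significant increases in adverse effects as further support for success.

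The Objectives section builds the same reasoning into the primary hypothesis, which expects "no significant differences in dropout rates, protocol adherence, or the incidence of adverse events (AEs) and serious adverse events (SAEs) between the two groups".

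Other text that bears on the point:
- Outcome measures and data collection lists tolerability and safety as the other primary outcome, beside HAM-D-17 change.
- Sample size: "A total of 60 participants (30 in the active arm and 30 in the sham arm) is planned". The calculation concerns HAM-D-17 only, with "a two-tailed significance level of 0.05, and 80% power". The section concedes limited power for some secondary and exploratory outcomes and does not mention AEs.
- Data analysis plan: AEs are compared by odds ratios with 95% confidence intervals.
- Success criteria, tolerability: absolute thresholds (dropout of at most 15%, at least 85% completing all sessions).
- Participant withdrawal and study termination: the study is paused for SAEs related to FES.

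No section gives an expected AE rate, a maximum acceptable rate or excess, or power for an AE comparison.

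**The concern.** A non-significant test says that the data are compatible with no difference. It does not say that they are incompatible with a harmful one. A rule that equates the two rewards imprecision: fewer participants or less complete AE data make a pass more likely whatever the true effect of the device.

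The rule decides one of the three success domains, on a primary outcome, and meeting the criteria is said to justify planning a large multisite trial. A real excess of AEs could therefore be labelled a safety success because the trial was too small to show it.

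The comparator adds a question of interpretation. Sham is itself electrical stimulation, at 1–8 mA, and the Intervention section accepts that it may cause some contractions. Similar rates in the two arms would not by themselves show that FES is free of stimulation-related AEs; the absolute rate in the active arm matters as well.

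**Working it through.** **Plan's own figure.** There is none to reproduce, because no power, margin or rate is stated for AEs. The check asks how often the rule would be met if active FES truly doubled the AE rate.

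**Inputs from the article.** 30 per arm (Sample size); 1:1 allocation (Randomization and masking); odds ratio with 95% CI for AEs (Data analysis plan).

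**Assumptions.** Two-sided 0.05 for AEs (the article states it for HAM-D-17 only). Each participant counts once, as having or not having the AE. Sham rate *p* from 5% to 40%, with the active rate at 2*p*. All 30 per arm are analysed. Only the frequency comparison is modelled.

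**Method.** Let X (active) follow Binomial(30, 2*p*) and Y (sham) follow Binomial(30, *p*). Then

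P(pass) = 1 − Σ P(X = x) · P(Y = y), summed over all (x, y) that the test calls significant.

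The article names no test, so three were enumerated exactly: Fisher, uncorrected chi-square, and the Wald 95% CI for the odds ratio (0.5 added to each cell when one is zero).

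| Sham vs active | Chi-square | Wald OR | Fisher | Range |
|---|---|---|---|---|
| 5% vs 10% | 89.4% | 98.5% | 98.1% | 89–99% |
| 10% vs 20% | 80.6% | 87.9% | 90.4% | 81–90% |
| 20% vs 40% | 60.8% | 63.5% | 70.2% | 61–70% |
| 25% vs 50% | 48.4% | 49.2% | 58.7% | 48–59% |
| 30% vs 60% | 33.7% | 33.8% | 43.9% | 34–44% |
| 40% vs 80% | 9.5% | 9.8% | 14.9% | 10–15% |

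The pass chance drops to 50% at a sham rate of about 25% (chi-square, Wald) to 28.5% (Fisher).

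**Effect of trial size.** With 25 per arm, close to the 51 expected completers, the pass chance rises: 83–91% at 10% vs 20%, 65–77% at 20% vs 40%, 38–49% at 30% vs 60%. The true excess is the same and the trial is smaller, yet success is likelier.

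**Size needed for 80% power to detect a doubling.** n per arm = [1.96·√(2p̄(1−p̄)) + 0.8416·√(p₁(1−p₁) + p₂(1−p₂))]² / (p₂−p₁)², where p̄ is the mean of the two rates.
- 10% vs 20%: (1.96·√0.255 + 0.8416·√0.25)² / 0.01 = 1.990 / 0.01, so 199.
- 20% vs 40%: (1.96·√0.42 + 0.8416·√0.40)² / 0.04 = 3.249 / 0.04, so 82.
- By the same formula, 42 at 30% vs 60% and 23 at 40% vs 80%.

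**Precision when the true rates are equal.** The half-width of the 95% CI for the risk difference is 1.96·√(2p(1−p)/30): 15 percentage points at p = 10%, 20 at 20% and 23 at 30%. A null result leaves differences of that order open.

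**Two observed results (active vs sham).**
- 12/30 vs 6/30. Fisher p = 0.16. Chi-square = 0.2² / (0.3·0.7·2/30) = 2.86, p = 0.09. OR = (12·24)/(18·6) = 2.67; SE of log OR = √(1/12 + 1/18 + 1/6 + 1/24) = 0.589; 95% CI 0.84 to 8.46. All three pass the rule.
- 5/30 vs 0/30. Fisher p = 0.052: pass. With 0.5 added, OR = (5.5·30.5)/(25.5·0.5) = 13.2, 95% CI 0.69 to 249: pass. Uncorrected chi-square = 5.45, p = 0.020: fail. The outcome depends on a test that the article does not name.

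**The case against.** A reader might infer that the trial would usually pass FES as safe whatever the AE rate, or that any clear excess of harm would be reported as success. The documents do not support either. They give no AE rate. AEs are queried daily over 20 sessions and recorded whatever their relation to FES, and sham is real stimulation, so the proportion with any AE could be high. At 30% or more in the sham arm a doubling would be detected more often than not. The rule also covers severity, a second comparison that could lower the pass chance somewhat. This stands and limits the claim. It does not rescue the rule, because less common events such as serious AEs may well lie in the low range, where the rule discriminates least.

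Other safeguards exist. Every AE is graded for severity and causality, odds ratios with intervals are planned, and related SAEs pause the study. These limit the consequence, but none sets an acceptable AE excess or alters the success rule.

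It is also tempting to say that dropout and adherence are judged by non-significance. The Objectives hypothesis is worded that way, but the Success criteria decide tolerability by absolute thresholds. For those outcomes the wording needs aligning; the decision rule is not at fault.

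Finally, this is a pilot, and success leads to another trial rather than to clinical use. That lowers the priority. However, a pilot can report safety descriptively, and this one sets a significance-based pass instead.

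**Conclusion.** The point holds in a conditional form. The safety criterion treats absence of significance as evidence of safety, with no margin and no AE power, and is easier to meet the smaller the trial. That flaw does not depend on any assumed rate.

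Its size does. With 30 per arm and two-sided 0.05, and ignoring the severity comparison, a doubled AE rate would pass more often than not for sham rates up to about 25%: 89–99% of the time at 5% vs 10%, falling to 48–59% at 25% vs 50%. At 30% vs 60% it would pass in 34–44% of trials and at 40% vs 80% in 10–15%.

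This should be fixed before results are known. It affects how a primary outcome is interpreted; randomisation, data collection and the planned estimates are untouched.

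**What to change.** - **Success criteria.** Delete the sentence that makes non-significance the mark of safety, and reword the later clause on significant increases in adverse effects to match.
- **Reporting.** Give per-arm rates of any, device-related, moderate or severe, and serious AEs, with the active-minus-sham risk difference and its 95% CI.
- **Decision.** Either judge the upper confidence limit against an acceptable excess that the sponsor sets in advance, or state that safety is descriptive and carries no pass or fail. Given half-widths of 15 to 23 points, a tight margin is unlikely to be met with 30 per arm, so the descriptive option may be the realistic one.
- **Objectives.** Reword the hypothesis on AEs and SAEs in the same way, and align its dropout and adherence wording with the absolute thresholds already in the Success criteria.

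Cost: wording in two sections and no new data, since AE severity and causality are already recorded and interval estimates are already planned. Recruitment is still under way, so the change can precede the results. The drawback is that the safety claim becomes harder to make.

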### Data analysis plan

Baseline demographic and clinical characteristics will be summarized for each treatment group. The primary analyses will be conducted on a modified intention-to-treat (ITT) sample, including all randomized participants who received at least one FES session. The efficacy of FES will be evaluated using ANCOVA to compare changes in HAM-D-17 scores from baseline to the final FES session between the active and sham groups, adjusting for baseline HAM-D-17 score and sex. Correlations between baseline and follow-up HAM-D-17 scores will be analyzed at the participant level. Similar analyses will be conducted for secondary clinical outcomes. Moreover, FES tolerability will be evaluated by summarizing overall dropout rates as counts and percentages. For dichotomous outcomes like remission, response, and AEs, between-group differences will be analyzed using odds ratios with 95% confidence intervals. Blinding effectiveness will be assessed by calculating Bang’s blinding index for rater and participants. Analyses stratified by sex and age will also be performed to explore potential subgroup differences.

Additionally, automated facial behavior analysis software (OpenFace) will be used to quantify Duchenne smile metrics derived from facial Action Units (AUs), including frequency, duration, and average activation intensity. Duchenne smiles will be identified based on the concurrent activation of AU12 (lip corner puller) and AU6 (cheek raiser). Descriptive statistics and group comparisons will be performed to examine differences in genuine smiling between the FES and sham groups. OpenFace is an open-source facial behavior analysis toolkit developed by researchers at the University of Cambridge and Carnegie Mellon University. Using computer vision and machine learning algorithms, it detects facial landmarks (e.g., eye, mouth, and eyebrow positions), estimates head pose, and quantifies facial muscle activity through the Facial Action Coding System (FACS) by identifying the presence and intensity of facial AUs. Participant videos will be processed using OpenFace to extract facial landmark coordinates and AU measurements. The output will consist of CSV files containing numerical facial behavioral data identified only by participants’ study IDs. These de-identified data will subsequently be used for statistical analysis.

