### Participant withdrawal and study termination

Participants may withdraw their consent and discontinue the study at any time without penalty. Withdrawal may also be initiated by the participant’s physician or the investigator if continued participation is deemed to pose a significant risk. Discontinuation criteria include a worsening of depression (defined as a more than 25% increase in QIDS-SR-16 score compared to baseline across two consecutive assessments), developing active suicidal intent, attempting suicide, non-adherence to study procedures, or missing more than two FES sessions. Participants meeting exclusion criteria during the trial will also be withdrawn. All early withdrawals will be documented, and participants will be asked to provide feedback on their FES experience and undergo any recommended medical evaluations. If study termination or early withdrawal is due to an AE or SAE, the research team will assist the participant in obtaining appropriate medical care, and the PI will conduct follow-up as required.

The study will be paused if SAEs related to FES are identified. Premature termination may occur if significant risks to participants, protocol non-adherence, insufficient evaluable data, or device modifications are identified. In such cases, the research ethics board will be informed.

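### A non-significant adverse-event comparison is counted as evidence of safety, in a trial of 30 per arm with no safety margin

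*Protocol article*

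**What the plan says.** Safety is part of the primary objective (protocol article, Objectives) and one of three domains on which the trial is judged (Success criteria). For that domain the article states that "no significant differences between groups in AE frequency or severity will indicate successful safety outcomes". Later in the same section, sustained benefit "without significant increases in adverse effects" is said to add to the trial's success. The hypothesis under Objectives expects "no significant differences in dropout rates, protocol adherence, or the incidence of adverse events (AEs) and serious adverse events (SAEs) between the two groups".

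The Sample size section justifies the number of participants by HAM-D-17: "A total of 60 participants (30 in the active arm and 30 in the sham arm) is planned". It gives no power, margin or precision target for AEs. Under Data analysis plan, for dichotomous outcomes including AEs, "between-group differences will be analyzed using odds ratios with 95% confidence intervals". Success criteria also says that the count, kind and duration of AEs will be looked at in both arms, and that meeting the criteria would support a larger multisite trial.

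**The concern.** A test that does not reject shows only that the data were too few or too variable to separate the arms. It does not show that the arms are alike. A rule that turns this into success rewards imprecision: the fewer the participants and the more incomplete the AE data, the easier it is to pass. It is weakest for uncommon events, which include the serious ones.

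The trial could therefore report a successful safety outcome, and carry it into the case for a multisite trial, while its own confidence interval still allows a several-fold excess in the odds of harm. This is not a detail left to a later analysis plan. The decision rule itself is stated, and it is the wrong rule.

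**Working it through.** **Inputs.** 30 per arm (Sample size). Two-sided 5% level, which the article states for efficacy and is assumed here for AEs. Odds ratio with 95% CI (Data analysis plan). The sham AE risk is not given, so a range is assumed. The article has no power figure for safety to reproduce. Its total of 60 is for HAM-D-17 and is used here only to fix n.

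**1. How often a true doubling would be non-significant.** Let X_A ~ Bin(30, 2p) and X_S ~ Bin(30, p). Sum P(X_A = a)·P(X_S = b) over all 31 × 31 tables that are non-significant, either by Fisher's test or because the Wald 95% CI for the odds ratio includes 1 (0.5 added to each cell if one is zero).

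| Sham vs active risk (assumed) | Fisher | Wald OR CI |
|---|---|---|
| 5% vs 10% | 98% | 99% |
| 10% vs 20% | 90% | 88% |
| 15% vs 30% | 81% | 75% |
| 20% vs 40% | 70% | 63% |
| 25% vs 50% | 59% | 49% |
| 30% vs 60% | 44% | 34% |
| 40% vs 80% | 15% | 10% |

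The 50% line is crossed at a sham risk of about 25% (Wald) to 28% (Fisher). Uncorrected chi-square gives 81% at 10% vs 20% and 61% at 20% vs 40%, so the choice of test does not alter the picture. Only the frequency comparison is modelled. The rule also requires no significant difference in severity, so these figures are upper bounds on the pass rate.

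**2. Single results that would pass on frequency.**
- 12/30 vs 6/30: OR = (12 × 24)/(18 × 6) = 2.67. SE of log OR = √(1/12 + 1/18 + 1/6 + 1/24) = 0.589. 95% CI = exp(0.981 ± 1.96 × 0.589) = 0.84 to 8.46. The risk difference is 20 points, with 95% CI 0.20 ± 1.96·√(0.24/30 + 0.16/30) = 0.20 ± 0.226, or about −3 to +43 points.
- 5/30 vs 0/30: Fisher p = 0.052. Corrected OR = (5.5 × 30.5)/(25.5 × 0.5) = 13.2, 95% CI 0.69 to 249. Uncorrected chi-square gives p = 0.020, so this is a boundary case.

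**3. What 30 per arm can exclude.** If the true risks are equal, the half-width of the 95% CI for the risk difference is 1.96·√(2p(1−p)/30): about 15 points at p = 10% and 20 points at p = 20%. With no events among 30 in one arm, the one-sided 95% upper bound is 1 − 0.05^(1/30) = 9.5%. Excluding an excess of 15 points (an assumed margin) at one-sided 0.025 with 80% power needs (1.96 + 0.84)²·2p(1−p)/0.15², which is 63 per arm at 10% and 112 at 20%.

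**The case against.** The best defence is that this is a proof-of-concept pilot. Meeting the criteria leads only to the design of a larger trial, and the odds ratios with confidence intervals will show readers how imprecise the comparison is. The kind and duration of AEs will also be examined. This stands, and it lowers the weight of the point. It does not repair the rule, because a reported success would still rest on non-significance.

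Four stronger readings are tempting, and the article does not support them.

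- *Any doubling of AE risk would usually pass.* This fails for common AEs, as the table shows. AEs are asked about daily over 20 stimulation sessions, so a high any-AE rate cannot be excluded.
- *Five SAEs against none would simply be reported as safe.* The result depends on the test, and six against none is significant by Fisher (p = 0.024). The article also says "The study will be paused if SAEs related to FES are identified", so related events would not go unremarked.
- *The pause rule contradicts the success rule.* It does not. One is a safeguard during the trial, the other a summary at its end.
- *Tolerability also passes by default.* Success criteria judges it by absolute thresholds: dropout of at most 15%, and at least 85% of participants completing all sessions. With true dropout of 15% and 30% in the two arms, overall dropout of at most 9 of 60 would occur in only about 10% of trials. Non-significance of dropout appears only in the hypothesis under Objectives.

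**Conclusion.** The concern holds for the AE and SAE comparison. As written, the plan accepts absence of significance as evidence of safety, with no margin and no sample size for that purpose. That fault in the inference does not depend on any assumed rate.

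Its size does. For a sham AE risk of 10 to 20%, a true doubling passes the frequency comparison in about 63 to 90% of trials (Fisher or Wald), and this is an upper bound for the whole rule. Above about 25 to 28% a doubling is more likely than not to be found. The point should be fixed, but it does not touch the primary efficacy analysis, and the trial is a pilot.

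**What to change.** - **Success criteria:** delete both statements that make the absence of a significant AE difference or increase a sign of success. State that a non-significant difference is not evidence of safety.
- **Objectives:** reword the hypothesis so that it no longer predicts non-significance. For example, say that AEs, SAEs, dropout and adherence will be estimated in each arm with 95% confidence intervals.
- **Data analysis plan:** report AE and SAE risks per arm with exact 95% CIs. Add the active-minus-sham risk difference with its 95% CI to the odds ratio already planned. List SAEs individually.
- **Safety label:** use the term successful only if the upper confidence limit of the difference falls below a margin that the sponsor fixes before unblinding. Otherwise call the result inconclusive. Step 3 of the working shows that 30 per arm will rarely exclude a tight margin, so plain description may be the realistic choice.
- **Tolerability:** leave the absolute thresholds as they are.

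The cost is wording in three sections, with no extra participants or data. The price is a more modest safety claim. Recruitment is already under way, so any margin should be set soon, while the data are still blinded.
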